**17b. Will pregnant or nursing mothers be included?**

Yes, possibly. There is no increased risk to pregnant women or breast-feeding mothers, and we see no reason not to include them.

**17c. Does your study involve invasive procedures such as blood taking, muscle biopsy or the administration of a medicinal product?**

No

**17d. If medical devices are to be used on any participant, do they comply with the requirements of the Medical Devices Directives?**

No; HoloLens 2 is not classified as a Medical Device.

**17e. List the locations or sites where the work will be done:**

Clinical Simulation Laboratory, Imperial College London, St Mary's Hospital, [name]

**17f. Will group or individual interviews/questionnaires discuss any topics or issues that might be sensitive, embarrassing or upsetting?**

No; simulated scenarios only.

**17g. Is it possible that criminal or other disclosures requiring action, e.g. evidence of professional misconduct, could be made during the study?**

No

**17h. Describe any expected benefits to the research participant**

No direct benefit to participants.

**17i. Under what circumstances might a participant not continue with the study, or the study be terminated in part or as a whole?**

Following wide-spread global commercial use of HoloLens across multiple sectors and industries there have been no recorded cases of harm coming to users.

If participants do not wish to complete the simulation, this will be facilitated, and no participants will be made to continue. If any participant wishes to withdraw, they will be able to stop and will not be coerced into continuing. Any identifiable data collected for a participant that withdraws from the study will be destroyed and not used for the purposes of analysis.

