2. Advanced Life Support: All participants will be provided with a refresher instruction on core aspects of advanced life support according Resuscitation Council UK guidelines. Instruction provided will cover all knowledge and practical skills required to successfully complete each of the simulated clinical scenarios, including advanced airway skills. Clinical scenario protocols will be written by experienced simulation practitioners and based upon the guidelines for the management of in-hospital assessment and resuscitation of the critically unwell patient.

**Simulation study method:** The study will be conducted according to a randomised cross-over design. Participants will complete two simulated clinical resuscitation scenarios as part of a single half-day study session that will also include their standardised training. There will

be a wash-out period of at least 1 hour between each scenario. This is a deliberately pragmatic methodological approach that has been chosen to ensure sufficient participant recruitment and study completion given time demands on participants if the study were to be split across multiple sessions. Prior to commencing the first simulated scenario participants will be randomly assigned to one of two groups - standard care, or HL2 supported care - and will cross-over into the alternate group for the second scenario. The order of the test scenarios will be counterbalanced to mitigate any learning effects. The order of HL2/standard care will be determined by using sealed envelopes prior to starting the simulation. Participants will be required to undertake advanced airway skills in order to test the impact of HL2 on remotely supporting the delivery of vital clinical skills in high stress situations. The clinical scenarios will not be identical but will be based upon standardised clinical moulages undertaken for basic and advanced life support qualifications, and those undertaken by doctors in training as part of their core curriculum to ensure consistency, reliability and control for learning effects.

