The simulation will be undertaken in a specialist simulation lab at Imperial College London facilitated and led by experienced simulation practitioners. The research team will be solely responsible for capturing observational data. A high-fidelity adult patient simulator (Laerdal) will be used to simulate an unwell adult with COVID-19. Vital signs will be standardized and pre-programmed with an adjustable override feature controlled by the study investigators. Before the start of each simulation session, study investigators will provide information to the participants on the patient using a standardised clinical moulage, with instructions to follow during the case, and the roles of study participants defined prior to the start of the simulation. Simulated medications, fluids, and equipment will all be available. Full PPE will also be available to all participants in the scenario. All scenarios will be video recorded, and these will subsequently be assessed by two independent researchers.

We aim to enrol 30 individual participants into the study who will undertake a total of 60 clinical scenarios (30 as standard care, 30 as HL2 supported care). The study will take place in a single setting - the study team anticipate this will last a maximum of 2hrs to allow for consent, initial technical training and the completion of 2x clinical scenarios.

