#### Outcome measures:

The primary outcome will be

- Error rate as assessed by the validated ICECAP Tool (Imperial College Error Capture Tool) a validated multi-dimensional assessment of error

Secondary outcomes will be

- Time to complete the clinical scenario
- Successful completion of the clinical scenario - as assessed by simulation team
- Global assessment of team performance - assessed using the validated OTAS Tool (Observational Teamwork Assessment for Surgery) and T-SAW-C Tool (Teamwork Skills Assessment for Ward Care)
- Errors in PPE use - assessed according to Public Health England (PHE) guidance and number of visor failures (e.g., inadvertent removal, misting, contamination or obstruction of clinical care)
- Participant stress/cognitive load - assessed via the validated NASA Task Load Index (NASA-TLX) and State Trait Anxiety Index (STAI) Tools
- Usability / technology feedback questionnaire for those wearing the HL2

All questionnaire items and assessment tools listed above are provided in the attached documents. Participant responses will be collected at the time of study completion, and assessment of video recordings will be undertaken during the data analysis stage of the study

**Statistical analysis:** Standard descriptive data will be employed. Independent two-sample t-tests will be calculated for normal continuous data, including ICECAP and OTAS scores, and time-to completion data. The Wilcoxon-Mann-Whitney U test will be used to analyse TLX scores. Multivariate linear regressions will be calculated to control for potential confounders and to assess association. Within subject comparisons will also be made to assess how the technology influences individual performance.

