**17. Participant Involvement: Risks, Requirements and Benefits**

**17a. Describe potential hazards, risks or adverse effects that may be associated with the study?**

The work will be performed within a simulated environment, where the risks to staff members are minimised. The major risk comes through the potential for COVID-19 transmission as described in section 11.

There is the possibility that a subject may feel uncomfortable or disorientated whilst wearing the HL2 device. If this occurs, then they will have the opportunity to stop the simulation and then either recover and carry on or withdraw from the study. Members of the simulation faculty and study team will be present throughout, and if there is any sign that subject are at risk of injury from becoming disorientated whilst wearing the device they will step in to stop the simulation and support the participant to prevent injury.

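### A participant who cannot continue because of the headset is offered only withdrawal, and the withdrawal rule then removes that failure from the HL2 comparison

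*Protocol*

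**What the plan says.** On withdrawal, section 17i of the Protocol states: "Any identifiable data collected for a participant that withdraws from the study will be destroyed and not used for the purposes of analysis". The same section says, in a separate sentence, that nobody will be made to finish a simulation they do not wish to finish.

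Section 17a names a device-related cause: "There is the possibility that a subject may feel uncomfortable or disorientated whilst wearing the HL2 device". If that happens, "they will have the opportunity to stop the simulation and then either recover and carry on or withdraw from the study". No third outcome is given for someone who cannot recover but is content to remain in the study.

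Section 10 fixes the design and the data flow:
- "The study will be conducted according to a randomised cross-over design", with the headset worn in only one of the two conditions.
- "We aim to enrol 30 individual participants into the study who will undertake a total of 60 clinical scenarios".
- The primary outcome is "Error rate as assessed by the validated ICECAP Tool".
- Every scenario is filmed, and "assessment of video recordings will be undertaken during the data analysis stage of the study".
- For the questionnaires, "Participant responses will be collected at the time of study completion".
- Scenario completion, judged by the simulation staff, and HL2 usability are secondary outcomes.

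No section says that a device-related withdrawal is counted by condition or enters the comparison as a non-completion.

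**The concern.** Read together, 17a and 17i send a participant who cannot tolerate the headset to withdrawal, and withdrawal to deletion. The deletion is not neutral between conditions, because nobody can be made unwell by a headset they are not wearing. The people removed are those in whom the device did worst.

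The Protocol's summary (section 3) gives technical feasibility of the headset as the aim, the hypothesis in section 10 is equivalence with standard practice, and section 13e says the pilot is to inform the power calculation of a later trial. Losing device failures biases the feasibility result towards the device. It also withholds from the later trial a figure it will need, namely attrition by condition and cause. A later analysis plan can define populations and missing-data rules, but it cannot restore recordings that were destroyed before anyone scored them.

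**Working it through.** **Inputs.** Section 10 gives N = 30 participants with two scenarios each. 30 × 2 = 60, which reproduces the Protocol's total (30 per condition). The Protocol gives no withdrawal rate, SD, margin or power, so the number of device-related withdrawals, k, is an assumption. I use k = 0 to 4.

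**Step 1: what the rule destroys.** Take a participant who stops during the HL2 scenario, cannot recover and withdraws.
- *HL2 first:* a partial HL2 recording exists and no standard-care scenario has been run. The partial recording is destroyed.
- *HL2 second:* a finished standard-care recording and a partial HL2 recording exist. Both are destroyed before scoring.
- *Either order:* the questionnaires would usually not exist, because they are collected at the end. That loss does not come from 17i.

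**Step 2: effect on HL2 completion.** Let c be the completion proportion among those who do not withdraw. If withdrawals are excluded, the analysed figure is c. If they count as not completed, it is c × (30 − k)/30.

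| k | c = 100%: analysed | c = 100%: counted | c = 90%: analysed | c = 90%: counted |
|---|---|---|---|---|
| 0 | 100% | 100% | 90% | 90.0% |
| 1 | 100% | 96.7% | 90% | 87.0% |
| 2 | 100% | 93.3% | 90% | 84.0% |
| 3 | 100% | 90.0% | 90% | 81.0% |
| 4 | 100% | 86.7% | 90% | 78.0% |

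For example, with k = 3 and c = 100%: 27/30 = 90.0%, an overstatement of 10.0 points.

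**Step 3: how likely is at least one?** With an assumed per-person risk p, the chance is 1 − (1 − p)^30. This gives 45.5% for p = 2%, 78.5% for p = 5% and 95.8% for p = 10%. At p = 0 it is zero, which the Protocol does not rule out.

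**Step 4: error scores.** If the k withdrawers' HL2 error scores would have differed from the rest by d SD, the hidden shift in the mean difference is k × d/30. With k = 3 and d between 1 and 2 SD in size, that is 0.10 to 0.20 SD. The sign of d is unknown. A participant in difficulty may make more errors, but a scenario cut short leaves less time to make them.

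**The case against.** The strongest reply is that this is an ordinary consent safeguard. Destroying identifiable data when someone withdraws is legitimate, and missing-data handling often belongs in an analysis plan that is not shown here. That stands as far as it goes. The point is not that the safeguard is wrong, but that 17a leaves no other route for someone the device has stopped.

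A reader might infer several stronger things that the Protocol does not support:
- *That stopping is already treated as withdrawing.* It is not. Section 17a separates the two, 17i has a sentence for each, and someone who stops, recovers and continues is untouched by the destruction rule.
- *That all data are destroyed.* The rule covers identifiable data. A completion rating by the simulation staff need not depend on the video and might survive in coded form. However, identifiable is not defined, section 19b keeps a master list linking codes to people, and no rule retains such a record.
- *That device failures vanish altogether.* Section 11d requires adverse events to be reported, so an episode of disorientation may be on file. It would sit outside the outcome comparison.
- *That both scenarios are always lost.* With HL2 first there is no second scenario to lose.
- *That lost precision is the main harm.* With k = 1 to 4 the standard error grows by √(30/(30 − k)), or 1.7% to 7.4%. Most of that would occur under any data rule, because someone who leaves mid-scenario never yields a complete pair.

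The expected number is also held down. Section 14b excludes people known not to tolerate a headset, and section 10 requires hands-on training and a competency check first. Zero such withdrawals is plausible.

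**Conclusion.** The point holds in this form: followed as written, 17a and 17i together selectively remove from the outcome comparison those participants whom the headset forces out. The bias can arise only from the HL2 condition. Its direction is clear for completion and tolerability, which are made to look better, and unclear for the primary error outcome.

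The size depends on an unknown count. With 0 to 4 such withdrawals among 30, HL2 completion is overstated by 0 to 13.3 points (100% − 86.7%) if everyone else completes. This assumes that the completion rating goes with the destroyed data or is excluded with the participant, which the wording permits but does not state outright. The consent form is not reproduced in the text available here and may already draw the distinction. If it does, 17a and 17i still need to match it.

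This does not invalidate the design, but it should be settled before the first participant consents, because destroyed recordings cannot be recovered.

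**What to change.** Amend 17a, 17i and the consent form to distinguish two events.

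1. **Stopping a scenario or session.** The participant stays in the analysis. Data already collected are kept and scored, with consent. An HL2 scenario stopped in this way counts as not completed. The reason is recorded by condition and by order.
2. **Withdrawing consent for data use.** Identifiable data are destroyed as now, but a non-identifiable count, the condition at the time and any reason given are reported.

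Because the direction for error scores is uncertain, scores from truncated scenarios should be identified as such when reported. A model that uses single completed periods is no substitute for this change: the Protocol specifies none, and the usual likelihood fit assumes data missing at random, which loss caused by the device need not satisfy.

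The cost is protocol and consent wording. The one real downside is that pseudonymised data are kept after a participant stops, which needs explicit consent. The change leaves untouched when, or by whom, a simulation is stopped, and the right to withdraw data.

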## 18. Financial Incentives, Expenses and Compensation

### 18a. Will travel expenses be given?

No expenses or other payments will be provided to participants or study team members.

### 18b. Is any financial or other reward, apart from travel expenses, being offered to participants?

No

### 18c. Has payment of the Experimental Test Allowance been considered (JSP 752, chap 10 section 3)? Yes, and deemed to be not applicable.

### 18d. If this is a study in collaboration with a commercial organisation

No.

## 19. Confidentiality, Anonymity and Data Storage

### 19a. What steps will be taken to ensure confidentiality

HL2 devices utilise up to date security procedures and protocols. They are remotely configured using the Microsoft 365 Admin Centre in conjunction with Microsoft Intune, and as such adopt multi-factor authentication when joining the Remote Assist / Teams tenant that will be deployed in this study. The use of strong passwords will be enforced, and on location the devices will connect to the local secure Wi-Fi network only after having been specifically white listed by MAC address. The network is typically secured using WPA2 with the use of Pre-Shared Key (PSK) authentication. The approach has been approved for use within secure NHS networks, and will be overseen and authorised by an appropriate responsible individual in the ICT department of each participating organisation.

Data from the original MR outputs will be uploaded securely to an instance of a UK/EU-hosted GDPR-compliant secure cloud storage service such as Microsoft Azure which is in use in both the NHS and UK Military. The storage, retention and audit of data will follow all local policies and procedures and will receive approval from the responsible data protection officer at Imperial College which will act as data controller for the purposes of this study.

The Chief Investigator will preserve the confidentiality of participants taking part in the study and is registered under the Data Protection Act.

### 19b. Give details of any anonymisation procedures to be used (if applicable)

Participants entered into the study will be given an anonymised code, and their personal details will not be stored. A single master list for the anonymised code will be kept securely by the CI.

### 19c. Who will have access to the records and resulting data?

The CI only.

The study may also be audited by a Quality Assurance representative of the RGIT (Research Governance and Integrity Team) at Imperial College London. All necessary data and documents will be made available for inspection. The study may be subject to inspection and audit by regulatory bodies to ensure adherence to GCP and the NHS Research Governance Framework for Health and Social Care.

### 19d. Where, and for how long, do you intend to store the Consent Forms and other records?

The original copy of the signed and dated informed consent form will be retained at the participating organisation and is subject to inspection by representatives of the Sponsor, or representatives from Regulatory Authorities. All data will be stored for a minimum of 10 years (or according to changes in regulatory requirements). Data generated by this work will be processed in accordance with the Data Protection Act 2018. Retention and analysis will be conducted with regard to all local policies relating to the collection, holding and disclosure of data relating to individuals. The Principal and Co-applicants will act as custodians of the data and be responsible for its security. The CI will ensure the continued storage of all relevant data and documentation, even if they leave the clinic/practice or retire before the end of the required storage period. Delegation will be documented in writing. Videos kept on the study hard drive within the department of surgery will be re-formatted and all copies of the videos will be destroyed on completion of the study.

**19e: Have the Consent Form(s) and Participant information been reviewed and confirmed to be DPA 2018/GDPR compliant in accordance with organisational arrangements?**

Yes.

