**6. Preferred Timetable**

**6a. Preferred Start Date:** 1st May 2021

**6b. Expected Date of Completion:** End of study definition is final participant visit

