### **DATA STORAGE AND RETENTION**

All data will be stored for a minimum of 10 years (or according to changes in regulatory requirements). Data generated by this work will be processed in accordance with the Data Protection Act 2018. Retention and analysis will be conducted with regard to all local policies relating to the collection, holding and disclosure of data relating to individuals. The Principal and Co-applicants will act as custodians of the data and be responsible for its security. The CI will ensure the continued storage of all relevant data and documentation, even if they leave the clinic/practice or retire before the end of the required storage period. Delegation will be documented in writing.

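### Sections 19c and 19d of the protocol do not fit the planned dual video assessment: access is limited to the chief investigator, and the videos may be destroyed before they are scored

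*Protocol*

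**What the plan says.** **Who assesses the recordings, and when.** Section 10 (Project Design) states: "All scenarios will be video recorded, and these will subsequently be assessed by two independent researchers". Under Outcome measures, the same section says that "assessment of video recordings will be undertaken during the data analysis stage of the study" and, separately, that "Participant responses will be collected at the time of study completion".

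**Who may see the data.** Section 19c asks who will have access to the records and the data that result, and names only the chief investigator. It then allows for sponsor audit and regulatory inspection. No assessor or analyst is listed.

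**When the recordings go.** Section 19d says that "all copies of the videos will be destroyed on completion of the study". The protocol defines the end of the study once, in section 6b under the expected date of completion: "End of study definition is final participant visit".

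**What is kept.** Section 12 (Data storage and retention) and section 19d both set a minimum of 10 years for all data, and both make the principal and co-applicants its custodians. The sentence on destroying the videos comes at the end of 19d.

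**What depends on the recordings.** The primary outcome is the error rate on the ICECAP tool. Team performance, rated with OTAS and T-SAW-C, is a secondary outcome. Section 10 plans 30 participants and 60 scenarios.

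**The concern.** The plan relies on a second, independent look at every scenario, made from video. That needs two things: the assessors must be able to open the recordings, and the recordings must still exist when they do so. Section 19c as worded denies the first to at least one assessor. Section 19d, read with section 6b, can deny the second.

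Destruction cannot be undone. If recordings go before they are scored, neither the scores nor the agreement between the two assessors can be recovered, and disputed ratings cannot be checked against source. Section 13e says the purpose of this pilot is to supply the basis for a power calculation for a later trial, so it needs well-documented primary-outcome data.

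This is not a detail that a protocol may leave to the statistical analysis plan. The protocol itself fixes the access, destruction and end-of-study rules, and they conflict with its own assessment plan. A team that scored the videos in the sensible way could find itself departing from its own confidentiality commitments.

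**Working it through.** The protocol gives no calculated figure on this point. The check is to set the rules side by side.

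**Access**

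1. Assessors required by section 10: two independent researchers.
2. People with access under section 19c: one, the chief investigator. The exceptions cover audit and inspection, not scoring.
3. Two different people cannot both be the chief investigator. Even if the chief investigator were one assessor, 2 − 1 = 1 required assessor would have no access.
4. Other text also assumes wider access. Sections 12 and 19d name the principal and co-applicants as custodians, and section 10 says "The research team will be solely responsible for capturing observational data". Neither amends 19c or names the assessors, so the conflict remains.

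**Timing**

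| Step | Source | Timing stated |
|---|---|---|
| End of study | 6b | Final participant visit |
| Videos destroyed | 19d | On completion of the study |
| Participant responses collected | 10, Outcome measures | On study completion |
| Videos assessed | 10, Outcome measures | Data analysis stage |

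1. Section 19d does not say what completion means. The only definition available is the one in 6b, which stands under a heading about the date of completion.
2. If that definition applies, the destruction rule takes effect at the last visit.
3. Section 10 sets video assessment apart from the collection of responses at completion and assigns it to the analysis stage. Any recording still unscored at the last visit would then be lost.

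**How many recordings**

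- 30 participants × 2 scenarios = 60 recordings.
- If k recordings have been scored by the last visit, 60 − k are lost on the literal reading. The range runs from 0 (k = 60) to 60 (k = 0). The protocol gives no schedule that would fix k.

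**Does the primary outcome come from the video?** No sentence says so. Outcome measures describes two ways of obtaining data, participant responses and video assessment, and ICECAP is an assessment of error rather than a participant response. Video scoring is therefore the likely source. The statement that the research team captures observational data leaves room for some live scoring. Even then, the promised assessment by two independent researchers would still depend on the recordings.

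**The case against.** The strongest reply concerns timing. Section 19d does not cite 6b, and section 10 calls analysis a stage of the study, so completion in 19d can naturally include it. The protocol also uses the term loosely: responses collected at study completion most plausibly means each participant's own completion, not the last participant's visit. Nothing prevents scoring while recruitment is still open, since section 10 requires only that assessment follow the recording. This stands. The destruction conflict arises on a literal reading and is not the only possible meaning.

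On access, it can be said that 19c is a short answer on a form, placed directly after the text on the master code list, and was never meant to abolish dual rating. That is probably right about intent. But the question put in 19c covers records and resulting data in general, and the answer is incompatible with two assessors. This part of the point survives in full.

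A reader might infer several stronger things that the documents do not support:

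- **That the primary outcome will be lost.** This assumes that ICECAP is scored only from video, that none is scored before the last visit, and that 6b governs 19d. The protocol states none of the three.
- **That independent raters fall from two to none.** The protocol does not define independence or say that the chief investigator could not be an assessor. The text shows only that at least one assessor is barred.
- **That the 10-year rule contradicts the destruction rule.** In 19d the specific sentence on videos follows the general rule and reads as an exception to it. One clarifying clause is enough.
- **That the end-of-study definition is wrong, or that the consent form must change.** A last-visit definition is not an error in itself, and the consent pages are not available for review.

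**Conclusion.** The point holds as an internal inconsistency that should be corrected before the first recording is made.

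- **Access (firm).** Section 19c contradicts section 10. At least one of the two required assessors has no permitted access. This needs no assumption beyond the two assessors being different people.
- **Destruction (conditional).** If completion in 19d takes its meaning from 6b, recordings unscored at the final visit are destroyed. The number at risk lies between 0 and 60, and 60 is the worst case.
- **What is at stake.** The independent dual assessment is at risk and, on the likely but unstated assumption that they are scored from video, so are the ICECAP and teamwork outcomes.

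No sample size, test or stated figure changes. This looks like a drafting fault that most teams would work around. The reason to act is that the loss would be irreversible and the correction is small.

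**What to change.** Two sections need new wording.

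1. **Section 19d.** Replace destruction at study completion with destruction after both assessors have scored every recording, the scores have been verified and the database has been locked. Add that the scores, not the videos, fall under the 10-year retention, so that the exception is explicit here and consistent with section 12.
2. **Section 19c.** List the two video assessors and the analyst beside the chief investigator, with access under the participant code. The master list stays with the chief investigator, as section 19b already provides.

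Section 6b needs no change, because the new wording of 19d removes the timing conflict whatever the end-of-study definition.

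The cost is a wording amendment to the protocol. The one real downside is that identifiable video is held somewhat longer.
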